#### Primary Clinical Endpoints

We will use the patient-reported outcome measures of pain intensity PainDETECT [50] and the Numeric Pain Rating Scale [31] for the highest, average (ie, pain experienced most of the time), and lowest pain intensity in the prior week. The Numeric Pain Rating Scale [31] and PainDETECT [50] will be assessed weekly during the Qigong or pain management survey intervention period and then monthly during the 6-month follow-up period.

#### Secondary Clinical Endpoints

To address whole-person health, all secondary outcomes, which are patient-reported outcome measures, will be assessed at 3 time points (baseline, after the intervention period, and at 6 months follow-up). In addition, we will perform EMA assessments 4 times per day for 3 weeks at baseline, during the last 3 weeks of the 12-week intervention, and during the last 3 weeks of the 6-month follow-up. The Fitbit Charge 6 smartwatch is worn all the time during the duration of the study to measure physical and emotional functioning as well as obtain objective measurements on sleep, activity, and other information such as heart rate and stress levels (heart rate variability–based measure).

##### Impact and Type of Pain (NINDS-CDE SCI)

The NINDS-CDE SCI International SCI Pain Basic Data Set Version 3.0 [51] assesses different types of pain, the body location, average pain intensity, and neuropathic pain interference with mood, activity, and sleep. NINDS-CDE SCI–recommended PainDETECT [50] helps identify neuropathic pain phenotypes [52].

##### Physical Functioning

NINDS-CDE SCI Functional Index/Assistive Technology measures function related to basic mobility, self-care, fine motor function, and ambulation [53]. For the Patient Specific Functional Scale, participants rate their ability to achieve 3 self-identified important functional activities or goals [54].

##### Emotional Functioning

Patient Health Questionnaire-2 is used to assess symptoms of depression in adults with SCI [55-58]. We will use the NINDS-CDE recommended SCI-Quality of Life measurement [59] subscales on pain behavior, positive affect, resilience, and ability to participate, to obtain a comprehensive view of the participant’s emotional functioning [59].

##### Global Improvement

The Initiative on Methods, Measurement, and Pain Assessment in Clinical Trials–recommended Patient Global Impression of Change provides a measurement system with scores ranging from 1 to 7 for how a participant evaluates changes in their status, with score 1 reflecting “very much improved,” and gradually decreasing to 4 reflecting “no change” and further down to 7 reflecting “very much worse” [60,61].

##### EMA Surveys

EMA surveys will be sent through text or email: 27 real-time questions total; 10-item Positive and Negative Affect Schedule-Short Form (PANAS-SF) [62], activity, sleep, stress, mind awareness, body awareness, pain interference, and agency (ie, control over life and control over pain) to explore the dynamics of neuropathic pain intensity in daily life [63]. Two cognitive tests will be conducted, with a duration of 30-90 seconds total: (1) attention and set-shifting: number and number/letter sequencing on a 4×4 grid, that is, 1, A, 2, B, 3... (2) spatial working memory test: remembering sequence + location of squares on a 4×4 grid. Providing EMA 4 times per day for 3 weeks is feasible in terms of participant burden, while at the same time providing enough data to perform personal causal modeling.

#### Objective Measurements of Sleep, Activity, and Other Information, Obtained With a Consumer Device, the Fitbit Charge 6 Watch

Our primary data will be physical activity (minutes), heart rate (every second), stress level (heart rate variability–based), and sleep (minutes). Participants will install the Fitbit app with their account and use the OAuth 1.0a protocol on a University of Minnesota website (developed by coauthor [name]) to authorize Fitbit to transfer data directly to our University of Minnesota server. Participants will leave the Fitbit app open in the background so data can be transmitted to our server. In this way, we can monitor that data is being received and that the device is being charged. [name] has used this method successfully in several studies [64,65].

Virtual delivery of questionnaires related to assessments or check-ins will be organized through our secure University of Minnesota Zoom. Participants will be encouraged to complete all scheduled virtual visits and assessments. However, missed sessions will be allowed and recorded and will not be considered protocol deviations. We had 100% adherence to Qigong training, assessments, and weekly check-ins through Zoom in our prior Qigong studies (IRB# STUDY00005656; IRB# STUDY00011997) in those who completed the study. If an EMA survey, pain management assessment, or weekly or monthly check-in is missed, measures will be taken to get the information later. There are no stop criteria for missed sessions or missed testing. The clinical trial will be completely remotely delivered.

### Statistical Analyses

#### Sample Size Calculation

We plan on recruiting 40 SCI stakeholders (aim 1) and 40 adults with SCI-related neuropathic pain (aim 2). Stakeholders not only include adults with SCI but also caregivers and health care professionals and any other stakeholder related to adults with SCI.

Aim 1 requires a qualitative analysis, and thus, power analysis is not calculated.

The sample size for aim 2 of 40 adults with SCI-related neuropathic pain is based on our estimated accrual and enrollment rates from our prior studies on related research. Due to the nature of a feasibility study, power calculations were not conducted. With N=40, we will be able to estimate a rate for the feasibility endpoints, for example, the dropout rate, of 80% with the margin of error of the 95% CI controlled at ±10%. Based on prior literature, the sample size is sufficient to provide reliable estimates of the mean and SD of pain (primary outcome) and other outcomes, to determine the required sample size for future large efficiency studies.

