## Methods

### Overall Study Design

For aim 1, we will hold community event meetings (ie, education and listening sessions) in town halls and health care settings for SCI stakeholders to share information about the research and hold listening sessions. We will organize focus groups and in-depth interviews using the Consolidated Framework for Implementation Research in the Twin Cities and in South Texas. We estimate we will have 3-5 attendees if on Zoom, and 5-8 attendees if in-person. We estimate holding 3 in-depth interviews with the most informative SCI stakeholders, to better understand the facilitators and barriers to remotely delivered Qigong practice, and identify which sociodemographic, behavioral, cultural, or structural factors facilitate or hinder participation in the study as a whole, including access to a computer, iPad, or smartphone and internet needed for Qigong practice or pain management through a Qualtrics survey, and remotely delivered questionnaires. If in person, the focus groups and interviews will be held in Minnesota (University of Minnesota–Twin Cities) and South Texas (University of Texas Rio Grande Valley [UTRGV]).

For aim 2, we will organize a feasibility phase I randomized controlled trial design where 40 adults with SCI-related neuropathic pain with at least 50% (n=20) with health disparities (racial or ethnic minorities, Veterans, or adults living in rural, underserved areas) are randomized to (experimental group) a Qigong introduction class and a 12-week remotely delivered Qigong intervention, with a 6-month follow-up, or (active comparison group) they complete daily 2-minute surveys to manage their pain sent through Qualtrics, with a 6-month follow-up.

Randomization will be generated by an independent biostatistician. The outcome assessors and the biostatistician on the study will be blinded to the group allocation. We have registered this clinical trial with the National Institutes of Health (NIH) clinical trials registry. Our feasibility pilot trial follows the guidelines according to the Obesity-Related Behavioral Intervention Trials model [29] and NCCIH [30]. Based on the guidelines, we developed aims, protocol, and the following a priori feasibility benchmarks to rigorously test the methodology and feasibility of the intervention before a larger effectiveness clinical trial is conducted.

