#### Feasibility Benchmarks

Our feasibility markers are consistent with models and guidelines for intervention development (Table 2) [29,42]. Based on prior publications [43-46], we will assess the following a priori feasibility markers.

**Table 2 table2:** Feasibility benchmarks.

	Feasibility item and details	Benchmark (go/no-go criteria)
Recruitment and enrollment	Assess recruitment rates (screens and enrollment per trimester, sex, and racial outcomes). Evaluate the recruitment rate for complete and incomplete SCI^a^. We aim to recruit 40 participants between mid-year 1 and year 2.	The proportion of potential participants contacted who agreed to participate: 80% is excellent and 70% good. Ratio of complete/incomplete SCI. We estimate recruitment of 30%-40% of adults with complete, 60%-70% with incomplete SCI. Reasons for (not) participating and information collected during focus groups or interviews will help delineate facilitators and barriers to participation, including computer or internet access.
Feasibility and acceptability of the study design	Attrition rates in the Qigong or pain management survey groups.	Proportion of people withdrawing from the interventions. Dropout due to unrelated reasons will count as part of the general attrition. A proportion of 90% is excellent, and 80% good.
Feasibility, adherence, and acceptability of the Qigong practice	Assess intervention adherence, average Qigong practice, at least 3×/week (123 minutes), pain management surveys (daily), and satisfaction with the Qigong practice or pain management surveys. Identify facilitators and barriers to practicing Qigong at home or completing the pain management surveys.	Weekly and monthly check-ins (reporting minutes/week of practice) to identify facilitators and barriers to pain management surveys or practicing Qigong. The Qualtrics website (for pain management surveys) or Spring Forest Qigong website (for Qigong practice) logs time and duration of video access. A Spring Forest Qigong-certified instructor will do a 1:1 Qigong session with each participant via Zoom monthly for quality control and to give guidance. Feasibility: Excellent: >80% participants practice at least 2×/week; good ≥70%. For the pain management survey: completion of surveys at least 5 out of 7 days. Dropout due to lack of interest will be counted as general attrition: 10% dropout is excellent, 20% is good.

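### The ±10-point margin stated for an 80% rate with N=40 should be about ±12 points, and benchmarks measured in one arm are less precise still

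*Protocol article*

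**What the plan says.** The Sample Size Calculation section bases the 40 participants of aim 2 on the accrual and enrolment that the team expects from its earlier studies. It adds: "Due to the nature of a feasibility study, power calculations were not conducted". It then states how precisely that number of participants estimates a feasibility rate: "for example, the dropout rate, of 80% with the margin of error of the 95% CI controlled at ±10" per cent. No other numerical precision is claimed for N=40.

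Table 2 (Feasibility Benchmarks) labels its criteria go/no-go and sets tiers 10 points apart. Recruitment is excellent at 80% and good at 70%. The attrition row gives 90% and 80%. For Qigong practice the criterion is: "Feasibility: Excellent: >80% participants practice at least 2×/week; good ≥70" per cent. The Data Analysis section estimates each rate from the participants who reach the benchmark.

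On allocation, the Overall Study Design section says that participants "are randomized to (experimental group) a Qigong introduction class and a 12-week remotely delivered Qigong intervention" or to the daily survey comparison. It gives no ratio.

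**The concern.** The sentence fixes every input needed to check it: N=40, a rate of 80%, a 95% interval and a margin of ±10. For a single proportion these four numbers do not agree. As no power calculation was made, this is the only figure that tells a reader how much N=40 can show, and estimating feasibility rates is the purpose of aim 2.

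What is at stake is how the benchmark results are read. The claimed margin equals one tier of Table 2, and the real one is larger. For criteria that only one arm can supply, such as Qigong practice at least twice a week, it is larger again.

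The example also calls the 80% a dropout rate. Table 2 treats 10% dropout as excellent and 20% as good, so 80% makes sense only as retention.

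**Working it through.** **Inputs.** From Sample Size Calculation: n = 40, p = 0.80, two-sided 95% interval (z = 1.96), stated half-width 0.10. From Overall Study Design: two arms, ratio not stated.

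**1. The plan's own figure.** Wald half-width = z × √(p(1 − p)/n).

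- p(1 − p) = 0.8 × 0.2 = 0.16
- √(0.16/40) = 0.0632
- 1.96 × 0.0632 = 0.124, or **±12.4 points**

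The stated ±10 is not reproduced. Reading the rate as 20% dropout gives 0.2 × 0.8 = 0.16 and the same result.

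**2. Other 95% methods, 32/40.**

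| Method | Half-width (points) | Interval |
|---|---|---|
| Wald | 12.4 | 67.6% to 92.4% |
| Wald with t quantile | 12.8 | |
| Wald with continuity correction | 13.7 | |
| Wilson | 12.1 | 65.2% to 89.5% |
| Agresti-Coull | 12.4 | |
| Jeffreys | 12.1 | |
| Exact (Clopper-Pearson) | 13.3 | 64.4% to 91.0% |

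None gives 10.

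**3. What would give ±10.**

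- Change n: n = 1.96² × 0.16/0.10² = 61.5, so 62 (about 60 by Wilson, about 70 by the exact method).
- Change the rate at n = 40: p(1 − p) = 0.10² × 40/1.96² = 0.104, so p = 0.88 or above, or 0.12 or below. At 90% the half-width is 1.96 × √(0.09/40) = 9.3 points.
- Change the confidence level at n = 40 and 80%: 0.10/0.0632 = 1.58, which is about 88.6% confidence. A 90% two-sided interval gives ±10.4. The text says 95%.

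**4. Benchmarks measurable in one arm, at 80%.** The arm sizes are assumed.

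| Arm size | 1.96 × √(0.16/n) |
|---|---|
| 15 | ±20.2 points |
| 20 (1:1) | ±17.5 points |
| 25 | ±15.7 points |

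At n = 20, an observed 16/20 has a Wilson interval of 58% to 92% and an exact interval of 56% to 94%. The direction does not depend on the ratio: at 80%, any arm smaller than 40 has a margin above ±12.4.

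**5. Against the tiers.** An observed 32/40 has an exact interval of 64% to 91%. On the 90/80 retention scale this runs from below good to excellent.

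**The case against.** The best defence is that nothing operational depends on this sentence. N was set from accrual, the margin only describes the result, and Table 2 compares observed rates with fixed cut-offs, not with confidence limits. All of that stands. So does the point that the overlap of tiers is visible from the protocol's own number: 80% ± 10 already runs from 70% to 90%. The error understates the overlap but does not create it.

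It is also fair that ±10 is not wrong everywhere. At 90% retention (10% dropout) N=40 gives ±9.3. The claim fails at the rate it names. The Results section reports 8 dropouts among 36 recruited for aim 2, or 22%, so the favourable range of 12% or lower cannot be taken for granted. The article does not say whether those 8 had been randomized.

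Three stronger readings are tempting, and the document does not support them.

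- *A reader might infer that the trial is too small and needs 62 participants.* N was not derived from the margin, so a wrong margin does not make N wrong.
- *A reader might infer that the plan misstates precision per arm.* It claims ±10 for N=40 only and makes no per-arm claim. The ±17.5 figure depends on an assumed 1:1 split and applies at rates near 80%. It does not carry over to the safety criterion of at most 10% of participants with Qigong-linked events, where n=20 gives 1.96 × √(0.09/20) = 13.1 points.
- *A reader might extend the criticism to the next sentence*, which says that "the sample size is sufficient to provide reliable estimates of the mean and SD of pain (primary outcome) and other outcomes". That is a qualitative statement resting on cited literature that is not at hand. It contains no number to be wrong, and how a later trial should allow for uncertainty in an SD is a matter for that trial.

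**Conclusion.** The stated precision is wrong as written. For N=40, a rate of 80% and a 95% interval, the half-width is about 12.4 points (12.1 to 13.7 across standard methods), not 10. This rests only on the protocol's own inputs and holds whether the rate is read as 80% retention or 20% dropout.

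The wider margin for one-arm benchmarks is a consequence worth stating, not a second error. Its size, about ±17.5 points at 80%, rests on the assumption of 20 per arm.

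Severity is moderate. The sample size, the cut-offs and the planned estimates do not change. What changes is how firmly a reader may treat an observed rate as falling in one tier and not the next.

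**What to change.** 1. Keep N=40 and restate the margin as about ±12 points for a rate of 80% (exact 95% CI for 32/40: 64% to 91%).
2. Add that benchmarks measurable in only one arm are less precise, giving the margin for the planned arm size: ±17.5 points at 80% if 20 per arm. State the allocation ratio on which it rests.
3. Report a 95% CI beside each rate in Table 2, by arm where the benchmark belongs to one arm, so that tiers 10 points apart are read with their real uncertainty.
4. Reconcile the 80% dropout wording with Table 2: either 80% retention or 20% dropout. The attrition row of Table 2 needs the same care, since it describes the proportion withdrawing but calls 90% excellent.

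The cost is a few lines of text and one extra column when the results are reported. No participants are added and no cut-off moves; the stated precision becomes somewhat less favourable.

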#### Data Analysis

The demographic variables and other baseline characteristics, including sex, race, and ethnicity, will be summarized using descriptive statistics, including mean, median, SD, IQR, minimum, and maximum. Rate parameters for the feasibility markers will be estimated based on the participants who achieved each benchmark. All quantitative variables, including primary and secondary outcomes, will be summarized using descriptive statistics. For longitudinal outcomes, missing data will not be imputed. Mean and SD will be calculated for each outcome at each time point. Means and SDs of across-time changes (eg, pre- vs post-Qigong or pain management survey changes) and correlations will be estimated for all participants, each group, or stratum that will be used for sample size determination in future studies. Mediation analyses will explore potential mediators among variables measured with the Fitbit device for the relation between Qigong practice or pain management surveys and changes in neuropathic pain. Descriptive and feasibility data related to adults with health disparities will be investigated. Missing data will not be imputed. The % missingness will be tabulated for each time point by group, and the mechanism of missingness will be identified.

The qualitative variables (eg, focus groups, interviews, weekly and monthly check-ins) will be recorded, transcribed, and managed using NVivo (Lumivero). Coded units will be sorted into categories and analyzed for recurrent themes or patterns. Emerging categories will be reviewed for alignment with the quantitative findings. These findings will serve to reach conclusions on the feasibility, acceptability, and satisfaction of adults with SCI-related neuropathic pain in study participation and performing Qigong practice or completing pain management surveys. We will also report on conclusions relevant to adults with health disparities.

The principal investigator and program and data manager will meet weekly, and the entire study staff will meet monthly to focus on the progress of the study until project completion. Issues requiring immediate attention across sites will be addressed either by phone, email, Zoom, or in person. The author order of publications will be based on the relative scientific contributions of the principal investigator and key personnel.

### Ethical Considerations

We follow the ethical guidelines of the Declaration of Helsinki. The University of Minnesota’s Institutional Review Board (IRB) approved the study (IRB#STUDY00022415). The study is registered at ClinicalTrial.gov (NCT06140355).

All protocol amendments will be submitted for IRB approval prior to implementation and communication with the participants. If applicable, a new consent form will be signed. New consent forms and protocol amendments will be sent to NCCIH at the time of yearly reporting. Prior to consenting, the consent form will be sent via an email link for review. Eligible participants will have a virtual visit with study staff to review the consent document and ask questions. We will maximize IRB-approved eConsenting and use consent through a legally authorized representative if the participant is physically unable to sign. We will not enroll minors or participants unable to consent due to an altered mental capacity.

We use the University of Minnesota Research Electronic Data Capture (REDCap) database to send out and have participants digitally sign the eConsent forms. REDCap uses a MySQL database via a secure web interface. All IRB rules and HIPAA (Health Insurance Portability and Accountability Act) rules protecting the participants’ rights and confidentiality of records will be followed.

The HIPAA-eConsent forms, electronic medical record information (if applicable), and assessment data will be entered into the password-secured REDCap. EMA surveys and pain management surveys are collected on Qualtrics, and the Qigong practice is logged and sent as a Microsoft Excel file to the principal investigator ([name]). Virtual delivery of patient-reported outcome measures will be organized through our secure University of Minnesota Zoom. Their responses, including those during the weekly and monthly phone calls, will be entered into the REDCap database. Data on REDCap will be verified by the research staff for completeness and accuracy.

Data integrity and privacy are ensured by attributing a unique study identification number to each participant. Only the principal investigator and approved research staff designees have access to the key, identifying participants with these codes. All data are stored on secure username and password-protected University of Minnesota servers, which are operated by the Academic Health Center’s Information Systems group, and backed up daily, weekly, and monthly. Their servers provide a stable, secure, well-maintained, and high-capacity data storage environment.

Data analysis (including assessments, notes, recordings, and NVivo analysis) is stored on the University of Minnesota secure box, with two-factor authentication. The Fitbit app on their smartphone will transmit data to the Fitbit server, which pushes data to a secure University of Minnesota server (monitored by coauthor [name]). Team members interacting with participants or their data completed the University of Minnesota’s training requirements for the Responsible Conduct of Research, Good Clinical Practice, HIPAA, data security, and study-specific training. They comply with all guidelines and maintain Good Clinical Practice training certificates every 3 years.

After study completion, deidentified data related to the outcomes of the aims of this project will be archived on the Dryad repository. The DOI link will be shared in the peer-reviewed publications together with the publication of the results of this study to ensure sufficient quality to validate and replicate research findings.

Regarding compensation, for aim 1, all participants receive US $50 when they complete either a focus group meeting or an interview. For aim 2, participants will receive a Fitbit that they can keep after the study ends. The participants in the Qigong group will also still have access to the Qigong video after the study has been completed. All participants receive US $200 at the end of the study and an additional US $1 for every EMA survey they have completed at the 3 time points during the study (maximum US $252).

Given that Qigong involves slow, gentle movements in standing, sitting, or lying positions, we do not expect any study-related adverse events from the treatment, similar to our experience in our preliminary studies [14,27]. We also do not expect any study-related adverse events with the pain management surveys. We will monitor adverse events weekly through direct check-in phone calls during the intervention period and monthly during the follow-up period and follow the Good Clinical Practice procedures.

Because there is minimal risk associated with this study, the IRB does not require a Clinical and Translational Science Institute data integrity monitor or data monitoring committee. The principal investigator ([name]) and [name] (study physician) will determine whether an adverse event is expected or unexpected, if it occurs. An adverse event will be considered unexpected if the nature, severity, or frequency of the event is not consistent with the risk information previously described for the study intervention. Aside from the weekly and monthly check-ins, we will ask participants to reach out to the principal investigator or project and data manager, if (severe) adverse events occur in the period between the calls. We will follow all regulations and protocols as outlined by the University of Minnesota’s IRB should this occur.

Our safety monitoring plan includes an independent medical monitor: [name], neurosurgeon at the University of Minnesota, is not associated with this research project and works independently of the principal investigator ([name]). He is not part of the key personnel involved in this grant, nor has he collaborated or copublished with the principal investigator within the past 3 years. He is qualified to review the patient safety data generated by this study because of his unique expertise as a neurosurgeon.

[name] will review all reported adverse events semiannually and as needed with the principal investigator ([name]) to review the number and type of adverse events. The principal investigator will inform [name] promptly of all study-related unanticipated problems involving risk to participants or others, serious adverse events, and all participants’ deaths associated with the protocol, and provide an unbiased written report of the event to the IRB. The medical monitor will comment on the outcomes of the event or problem, and in the case of a serious adverse event or death, comment on the relationship to participation in the study. The medical monitor will also indicate whether he concurs with the details of the report provided by the study investigator. Reports for events determined by either the investigator or medical monitor to be possibly or definitely related to study participation, and reports of events resulting in death, will be promptly forwarded to the University of Minnesota’s IRB and NCCIH.

